#### **3.2 Recruitment**

It is planned to recruit a maximum of 40 patients over a 15 months period.

Patients will be recruited after screening only if all inclusion criteria are met, no exclusion criteria are met and written informed consent has been obtained. No difference in recruitment concerning gender will be applied. According to the distribution of NSCLC more male than female study participants are expected.

### **3.3 Duration of the study**

The expected duration from beginning of recruitment to final data analysis will be 33 months (15 months recruitment, 15 months treatment (6 weeks for each patient, further treatment after 6 weeks is not part of the study), 18 months follow-up).

First patient in: 1.10.07; Last patient out: 15.2.2009, Closure of the database: 15.8.2010

### **3.4 Termination of protocol treatment**

The patient can discontinue trial participation at his/her own wish at any time. Protocol treatment can be terminated based upon the decision of the treating physician, due to unacceptable toxicity, progression, serious intercurrent disease or pregnancy. In any case, following a formal or an actual termination, the patient's follow up should be documented.

### **3.5 Early termination of trial**

The trial can be terminated early by the principal investigator in consultation with the co-investigators, if the formal termination criterion is reached or if patients' safety appears to be at risk. In case of termination of the trial the review board will be informed.

## **4 ENROLLMENT**

### **4.1 Inclusion criteria**

1. First diagnosis of histologically proven non-small cell lung cancer stage IIIB/IV
2. Tumor tissue available and suitable for EGFR gene resequencing
3. At least one measurable lesion according to RECIST
4. No prior standard chemotherapy, immunotherapy or small-molecules therapy
5.  $\geq 18$  years of age
6. ECOG performance status 0-2
7. Patient's own, written informed consent to participate in the trial
8. TSH, FT3 and FT4 serum levels compatible with contrast enhanced CT  
(no signs of hyperthyroidism)
9. Renal laboratory parameters compatible with contrast enhanced CT  
(serum creatinine  $\leq 1,7$  mg/dl)
10. No decompensated liver failure
11. No decompensated heart failure
12. No clinical or radiological sign of interstitial lung disease, no interstitial lung disease in the past
13. Life expectancy  $> 3$  months
14. In case of female patients with childbearing potential:
  - negative pregnancy test
  - effective method of contraception

## **4.2 Exclusion criteria**

1. Lack of appropriate biopsy specimen for EGFR gene re-sequencing
2. Previous systemic treatment of NSCLC (chemotherapy, immune therapy, therapy with small molecules and others)
3. Concurrent systemic immune therapy, chemotherapy, or therapy with any anticancer drug not indicated in the study protocol
4. Solitary metastases accessible to surgical resection
5. Bone metastases which have to be treated by radiotherapy (e.g. impending fracture), if no additional metastases outside the radiation field are present
6. Tumor masses with acute risk of life-threatening complications (e.g. compression of large arteries or trachea) which require emergency treatment (e.g. radiotherapy)
7. Malignant disease other than NSCLC within the last 5 years  
(exceptions: basalioma, carcinoma in situ of the cervix uteri, completely resected melanoma pT1N0M0 (Clark level II))
8. Infection with HIV, Hepatitis B, Hepatitis C
9. Patient's lack of accountability, inability to appreciate the nature, meaning and consequences of the trial and to formulate his/her own wishes adequately
10. Any medical, mental or psychological condition which in the opinion of the investigator would not permit the patient to complete the study or understand the patient information
11. Any person being in an institution on assignment of the respective authority
12. Simultaneous participation in any other clinical trial
13. Pregnancy, lactation
14. Diabetes mellitus
15. Elevated fasting blood glucose levels > 130 mg/dl (exception: reduction of an unexpectedly high blood glucose level to a value ≤ 130 mg/dl using regular insulin)

## **5 INDIVIDUAL TRIAL PROCEDURE**

### **5.1 Diagnosis and allocation to trial**

#### **Pathological diagnosis**

Diagnosis of NSCLC will be made/confirmed in the Institute for Pathology, University Clinic Cologne.

#### **Procurement of biopsy material for biological analyses**

In case of study inclusion material that is not required for histological diagnosis will be stored under the respective conditions (room temperature for paraffin-embedded tissue, -80° C in a

phone-alarm secured freezer in a local tissue bank of MTBTI in case of frozen or fresh material).

The following persons are responsible for the safe processing and storage of all biological material obtained during the study:

## **5.3 Mutation analysis**

Processing of tissue will be performed according to standard operating procedures (SOPs) established in MTBTI. Pretreatment biopsy material (tumor purity >70%, alternatively: tumor cell enrichment by microdissection) will be analyzed for EGFR mutational status by exon sequencing. A PCR has been established that allows for amplification and direct sequencing of EGFR mutational hotspots in exons 18, 19 and 21 from paraffin-embedded tumor tissue. Further a PCR amplification of KRAS exon 2 was established in the MTBTI (Zander et al. in preparation). In control experiments that were carried out on non-selected paraffin-embedded lung cancer specimens from a local tissue bank, PCR efficiency for all target amplicons was 100%. Target sequences will be amplified by single-round PCR. Purified PCR products will be bi-directionally sequenced (sequences controlled for bi-allelic target amplification; quality threshold: Phred score >30). Electropherograms will be manually and computationally (software: DNAsis) compared to germline sequences. In those tumors where tumor cell purity is estimated to be <70%, tumor cells will be enriched by laser-assisted microdissection (PALM system, available through a close collaboration with the Institute of Pathology, University of Cologne). All technology is established in the MTBTI laboratories and there is extensive experience with generating and evaluating molecular genetic data.

## **5.4 EGFR immunohistochemistry**

A positive correlation between EGFR positivity in immunohistochemistry and response to therapy has been demonstrated in relapsed NSCLC patients treated with erlotinib in the BR.21 phase III trial (Shepherd et al., 2005). Therefore, EGFR expression in primary paraffin embedded tumor tissue will be analyzed. EGFR staining will be performed in the Institute of

Pathology of the University Hospital Cologne following standardized procedures established for clinical application.

## **5.5 Pre-Study Screening (staging examination)**

Within a maximum of 14 days prior to registration, all patients will be screened by the investigator. Each patient must provide a written informed consent to the trial procedures. The patient must be informed about the study verbally and by the patient information by the principal investigator or one of the co-investigators, before informed consent is obtained. After obtaining written informed consent, the patient will be screened for eligibility. The following will be assessed:

- Patient demography
- Clinical examination including physical examination:
  - height, weight, vital signs, ECOG performance status
- Assessment of the neurological status
- Existing signs and symptoms
- Medical history (including concurrent illnesses) and review of all diagnostic procedures already performed for first diagnosis and staging of NSCLC
- Previous anti-cancer therapies and their outcome
- Concomitant medication
- Laboratory assessment including:
  - blood count including differential count
  - serum electrolytes (Na, K, Ca),
  - serum liver function parameters (total bilirubin, ASAT, ALAT, AP,  $\gamma$ GT, LDH),
  - serum renal function parameters (creatinine, BUN, uric acid),
  - serum TSH, FT3, FT4
  - total serum protein
  - ESR
  - blood coagulation parameters (Quick, PTT, Fibrinogen),
  - screening for infection with HIV1/2, hepatitis B, hepatitis C
  - CYFRA 21-1, CEA
  - fasting glucose level
  - pregnancy test for women with childbearing potential
- MRT or CT scan of the skull
- Electrocardiography (ECG)
- Cardiac function (LVEF) by echocardiography
- Pulmonary function (PO2, PCO2, DCO, vital capacity FEV1)
- FDG- and FLT-PET (s. table below)

- CT scans of all involved areas, as indicated in preexisting diagnostic procedures or PET analyses (s. table below).

**Table 1. Schedule for CT, FDG-PET and FLT-PET imaging.**

| Time point                             | Imaging of involved areas       |
|----------------------------------------|---------------------------------|
| Between d-10 and d1 (prior to therapy) | FDG-PET, FLT-PET, CT            |
| Day 1                                  | Start of therapy with erlotinib |
| Between d7 and d14                     | FDG-PET and FLT-PET             |
| Week 7                                 | FDG-PET, FDG-PET, CT            |

## 5.6 PET

### Patient preparation

For FDG-PET patients must refrain from ingestion for 12 hours prior to the PET examination; only the ingestion of carbohydrate-free drinks is permitted. The current glucose level should be measured before starting PET. Fasting glucose level over 130 mg/dl or known diabetes mellitus are exclusion criteria. Optionally regular insulin (e.g. 2 units) may be administered if blood sugars are unexpectedly high, provided that monitoring and emergency care are assured. For FLT-PET no special preparation is necessary.

### Administration of tracers, scanning and data evaluation

F-FDG and F-FLT will be synthesized at the Max-Planck-Institute for Neurological Research at the University of Cologne following standard procedures. A dose of 370 MBq FDG and 300 MBq FLT will be injected intravenously for whole-body examination by PET. Scanning will commence ~45-60 minutes after injection of tracers. PET instruments with full-ring detectors will be applied. Emission data will be corrected for attenuation, scatter and random and will be reconstructed to plains of 3.125 mm width and 128x128 voxels. For quantification of tracer uptake, standard methods, such as standardized uptake values (SUV) will be applied.

**Applied dose in each PET analysis:**

| Total activity for the respective RP | ED due to application of the RP | ED due to application of ALL the RP's | ED of all TM's | Allover ED                                 |
|--------------------------------------|---------------------------------|---------------------------------------|----------------|--------------------------------------------|
| Max. 370 MBq FDG
Day -4           | 7,0 mSv                         | 7 mSv                                 | 0,1 mS         | 7,1 mSv                             |
| Max. 300 MBq FLT
Day -3           | 9,9 mSv (f)
8,4 mSv (m)      | 16,9 mSv (f)
15,4 mSv (m)          | 0,1 mSv        | 17,0 mSv (f)
15,5 mSv (m) |
| Max. 370 MBq FDG
Day +8           | 7,0 mSv                         | 23,9 mSv (f)
22,4 mS (m)           | 0,1 mS         | 24,0 mSv
22,5 mSv         |
| Max. 300 MBq FLT
Day +9           | 9,9 mSv (f)
8,4 mSv (f)      | 33,8 mSv (f)
30,8 mSv (m)          | 0,1 mSv        | 33,9 mSv
30,9 mSv         |
| Max. 370 MBq FDG
Week 7           | 7,0 mSv                         | 40,8 mSv (f)
37,8 mSv (m)          | 0,1 mS         | 40,9 mSv
37,9 mSv         |
| Max. 300 MBq FLT
Week 7           | 9,9 (f) mSv
8,4 (m) mSv      | 50,7 mSv (f)
46,2 mSv (m)          | 0,1 mSv        | 50,8 mSv (f)
46,3 mSv (m) |

The used dose is the minimal dose to obtain high quality data suitable for further analysis

**5.7 Patient briefing and termination of protocol treatment**

After completion of staging, the patient is informed about the trial, including the following aspects: title and aim of the trial, nature of the treatment, side effects, reason for recruitment, passing on of data and material samples, insurance, the ethics committee vote and the patient's freedom to decide. The patient receives an information brochure and an informed consent form.

The signed original consent form and the record of the briefing remain in the patient's files. The patient will receive a copy of each document.

The patient can make a free decision on participation in the trial at any time. If trial participation is refused, the treatment can be freely chosen in accordance with the treating physician.

Termination of protocol treatment can occur at the patient's wish or if the treating physician decides to terminate it due to unacceptable toxicity, serious concurrent disease or pregnancy. Documentation after termination will be performed

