**Informed consent**

The investigator assumes the responsibility of obtaining written informed consent for each patient or the patient's legally authorized representative before any trial-specific procedures are performed and before any trial drug is administered.

Patients meeting the criteria set forth in the protocol will be offered the opportunity to participate in the trial. To avoid introduction of bias, the investigator must exercise no selectivity with regard to offering eligible patients the opportunity to participate in the trial. Patients or parents/legal guardians of all candidate patients will receive a comprehensive explanation of the proposed treatment, including the nature of the therapy, alternative therapies available, any known previously experienced adverse reactions, the investigational status of the trial drug, and other factors that are part of obtaining a proper informed consent. Patients will be given the opportunity to ask questions concerning the trial, and adequate time to consider their decision to or not to participate.

Informed consent will be documented by the use of a written consent form that includes all the elements required by regulations and ICH guidelines. The form is to be signed and dated by the patient or patient's legally authorized representative and by the person who administers the consent process. A copy of the signed form will be given to the person who signed it, the original signed consent form will be filed with the patient's medical records. The date and time of the informed consent must be recorded in the source documents.

If an amendment to the protocol changes the patient participation schedule in scope or activity, or increases the potential risk to the patient, the informed consent document must be revised, submitted to the EC for review and approved by the EC before use. The revised informed consent document must be used to obtain re-consent from any patients currently enrolled in the trial if the patient is affected by the amendment, and must be used to document consent from any new patients enrolled after the approval date of the amendment.

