## **5.8 Enrollment into the trial**

### **Reporting and recruitment**

If after completion of staging the patient is qualified for the trial and he/she gives written informed consent, recruitment will be performed by LCGC in Köln. For recruitment, the following is required:

- all entry criteria satisfied;
- no exclusion criterion satisfied;
- staging procedures completed according to protocol.

Patients should be asked to agree to be contacted by the trials coordination center.

This agreement and the patient's address are to be recorded on the REG form.

Patients who wish to avoid sending their personal data to the trials coordination center may be enrolled anonymously under a pseudonym code. Prerequisite for anonymous enrollment is, however, commitment to follow-up and documentation.

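### Section 5.7 opens by placing patient information after staging, but Section 5.5 counts both baseline PET scans as staging and requires written consent first

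*Protocol*

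**What the plan says.** The protocol describes the timing of information and consent in four places.

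- **Section 5.5**, Pre-Study Screening (staging examination), requires verbal and written information by the principal investigator or a co-investigator, then consent, then screening: "After obtaining written informed consent, the patient will be screened for eligibility". The list that follows includes the baseline FDG-PET and FLT-PET, which Table 1 places between day -10 and day 1, before therapy.
- **Section 5.7, opening paragraph**, gives another order: "After completion of staging, the patient is informed about the trial". It continues: "The patient receives an information brochure and an informed consent form". The same section then provides for the patient who refuses.
- **Section 5.7, Informed consent**, makes the investigator responsible for written consent "before any trial-specific procedures are performed and before any trial drug is administered".
- **Section 5.8, Reporting and recruitment**, states: "If after completion of staging the patient is qualified for the trial and he/she gives written informed consent, recruitment will be performed by LCGC". It also lists staging completed as the protocol requires among the conditions for recruitment.

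On who may consent, inclusion criterion 7 in Section 4.1 asks for "Patient's own, written informed consent to participate in the trial". The Informed consent subsection also accepts a legally authorized representative and says: "Patients or parents/legal guardians of all candidate patients will receive a comprehensive explanation".

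**The concern.** The opening of 5.7 dates the first information about the trial, not only the signature, and places it after staging. If staging has the meaning that the heading of 5.5 gives it, both tracers have been injected by then. A patient who declines at that step, or who proves ineligible, would have received the baseline radiation dose for a trial not yet explained. Section 5.7 is also the section on patient briefing, so it is where site staff would naturally look for when to inform.

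Baseline scans obtained before consent could also be challenged later. That would matter for the secondary objectives in Section 3.1 that rest on changes in SUV during treatment, since a change needs a pre-treatment value.

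**Working it through.** No power or error-rate figure bears on this point. The check compares the sections and does one piece of arithmetic on dose.

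**1. What staging means.** The heading of 5.5 equates pre-study screening with the staging examination, and 5.8 asks for staging completed as the protocol requires. No other set of staging procedures is defined. Both baseline PET scans are on the 5.5 list, so staging is not complete until both have been done.

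**2. The orders side by side.**

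| Place | Order |
|---|---|
| 5.5 | information → written consent → staging, including both PET scans |
| 5.7, Informed consent | written consent → any trial-specific procedure |
| 5.7, opening | staging → information, brochure and consent form |
| 5.8 | staging complete, patient qualified and consenting → recruitment; time of signature not fixed |

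The first and third rows exclude each other. The second and third exclude each other if at least one baseline PET scan is trial-specific.

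**3. Whether the baseline PET is trial-specific.** Section 9 says that approval of the radiation safety authority will be obtained for PET, and contrasts this with other radiation (radiotherapy, X-rays), which it places within usual care. Section 1.4 describes FDG-PET as part of a guideline work-up for lung cancer, so FDG-PET alone might be argued to be routine. Nothing in the protocol presents FLT-PET in that way. The conflict is therefore firm for FLT.

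**4. Dose that could precede information** (dose table in Section 5.6, which lists the baseline scans at days -4 and -3).

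- Women: FDG 7.0 + FLT 9.9 = 16.9 mSv. Adding the table's 0.1 mSv gives 17.0 mSv, the table's own figure.
- Men: FDG 7.0 + FLT 8.4 = 15.4 mSv. Adding 0.1 mSv gives 15.5 mSv, again the table's figure.
- Share of the study total: women 17.0 / 50.8 = 0.335; men 15.5 / 46.3 = 0.335.

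About one third is what two of six scans, one of three equal pairs, should give. The figure is simply the baseline dose; it does not estimate how many patients would be exposed before consent.

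**5. Who may consent.** Entry requires age 18 or over and the patient's own consent (Section 4.1, items 5 and 7). Exclusion criterion 9 in Section 4.2 removes patients who cannot form and express their own wishes. The representative, parent and guardian wording thus describes nobody who can enter the trial.

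**The case against.** **The right order is stated twice.** Section 5.5 and the Informed consent subsection both put consent first, and the latter stands within 5.7 itself. The trial has one centre, and 5.5 gives the information talk to the principal investigator or a co-investigator. A reader might infer that every one of the 40 patients, and every screen failure, would be scanned before consent. The protocol does not support that: a site following 5.5 would not do so. This objection stands in full against any claim of certain exposure. It does not remove the contradiction, because the opening of 5.7 still instructs otherwise.

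**Staging may mean the routine work-up.** Section 5.5 itself mentions procedures already performed for first diagnosis and staging, and stage IIIB/IV is an entry criterion. On that reading, 5.7 means only that patients are approached once advanced disease is known. This is possible, but the heading of 5.5 tells against it, and the text nowhere separates the two senses. It is a reason to clarify.

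**Section 5.8 may only list conditions for registration.** A reader might count 5.8 as a second contradiction. Its wording, "If after completion of staging the patient is qualified for the trial and he/she gives written informed consent", can equally mean that consent is on file when the patient is registered. Since 5.5 places screening within 14 days before registration, that reading fits. Section 5.8 is ambiguous and no more.

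**The harm to data is not shown.** A reader might infer that the scans would be unusable and the primary analysis lost. No section says scans would be discarded. The primary objective in Section 3.1 refers to ROC analysis of the SUV; changes in SUV are named under the secondary objectives. Nor does the protocol label the HIV and hepatitis tests trial-specific; they are on the screening list and serve exclusion criterion 8. These points stand, so the case rests on the PET scans.

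**Not everything can be seen.** The flowsheet in Section 0.4 is not shown, and most briefing and consent pages were removed from the copy reviewed. They may bear on the order intended, but could not make the two sentences agree.

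**Conclusion.** The opening of 5.7 is wrong as written. It cannot be followed together with 5.5, nor with the Informed consent subsection so long as at least the FLT-PET is trial-specific, as Section 9 indicates.

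Its size is a potential exposure before information and consent of up to 17.0 mSv in women and 15.5 mSv in men, about one third of the study total, for any patient handled by the literal wording of 5.7. The conclusion assumes that staging in 5.7 has the meaning given by the heading of 5.5. How many patients, if any, would be affected cannot be derived from the protocol. The statistical design is untouched. The point deserves correction because it concerns consent before tracer injection and the remedy is cheap.

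The representative and parent wording is a separate, minor inconsistency that looks like template text. A reader might infer that patients unable to consent could be enrolled; inclusion criterion 7, the age limit and exclusion criterion 9 already prevent that.

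**What to change.** - **Section 5.7, opening:** reconcile with 5.5 and the Informed consent subsection, so that information, hand-over of the form and written consent come before the trial-specific examinations listed in 5.5, at least the baseline FDG- and FLT-PET. If the routine diagnostic work-up was meant, say so and use a term other than staging.
- **Section 5.8:** state that written consent is already on file from before screening, and that completed staging confirms eligibility for registration.
- **Section 5.7, Informed consent (tidy-up):** align the representative, parent and guardian wording with inclusion criterion 7 and exclusion criterion 9.
- **Flowsheet and briefing guide:** check that both show the same order.

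The cost is a few sentences in two sections. Visits, scans, sample size and analysis stay as they are.
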